**Appendix 1. Quality of life questionnaires 23**

**Appendix 2. Laoratory tests for Procel 28**

**SUMMARY**

**Study title: Perioperative propranolol and celecoxib in stage III melanoma (ProCel)**

**Objectives**

**Primary Objective**

**To determine the effect of perioperative propranolol and celecoxib on tumoral immune cell infiltrates and proliferation and apoptosis markers in nodal and cutaneous metastatic melanoma compared to control.**

**Secondary Objectives**

To determine the safety and tolerability of the perioperative propranolol and celecoxib (ProCel) regimen

To assess changes in blood markers of inflammation and immunity in ProCel patients versus controls

**Study Design**

Prospective randomised controlled study; patients will be randomised to receive either the ProCel regimen perioperatively (stratified for ±systemic immunotherapy, metastatic site ie node, skin) or no ProCel regimen. For this pilot study placebo tablets will not be used and blinding is not possible for treating clinicians or participants. Investigators analysing tumour tissue and blood samples will be blinded to allocation.

**Planned Sample Size**

**N=40** participants, randomised to receive either the ProCel regimen or standard care.

**Inclusion Criteria**

This investigator-initiated study will be conducted through the Melanoma and Surgical Oncology Clinics at Royal Prince Alfred Hospital and Poche Centre North Sydney. Participants will be attendees of the clinics with histologically confirmed macroscopic nodal or cutaneous melanoma (in transit) metastases awaiting surgery for those metastases. Tumour banked specimens from previous biopsies and surgeries performed on a participant’s melanoma will be accessed from the Melanoma Institute Australia Tumour Bank.

**Study procedure**

Stage III metastatic melanoma in nodes and/or skin (in transit disease)

2 x baseline 2mm^2^ core biopsies of nodes and/or skin (allowing 2 x 1mm^2^ cores from each sample for tissue microarrayanalysis for proliferative, immune and inflammatory markers)

**Baseline**

**bloods, inflammatory**

**and immune markers**

**within 4 weeks of**

**study commencement**

**Randomised 1:1**

Treatment arm: 20 day ProCel regimen for 5d preoperatively, operative day and 14d postoperatively

Control arm

Surgical excision of metastasis as per clinical practice with routine paraffin sections and 1mm^2^ cores x 2 from each sample for tissue microarray analysis for proliferative, immune and inflammatory markers

Bloods for inflammatory and immune markers 2 weeks postoperatively

**Statistical considerations**

**Sample size calculation**: N=40; randomised 1:1 to ProCel or control arms

**Randomised controlled study**

**Duration of the Study** 24 months

# **1. BACKGROUND AND INTRODUCTION**

### **1.1. Stage III metastatic melanoma**

The presence of lymph node metastases or in transit metastases (metastases between the primary melanoma site and local lymph node field) in cutaneous melanoma patients is associated with five-year survival rates ranging from 93% in surgically resected American Joint Committee on Cancer (AJCC 8^th^ edition) stage IIIA disease to 32% for patients with resected stage IIID melanoma^1^. Particularly for stage IIIC and IIID patients the prognosis is dismal. The use of adjuvant drug therapy in the form of BRAF/MEK inhibitors or immunotherapy have improved prognosis, albeit with significant monetary cost and potentially toxic side effects. There is a however, still a need for further improvement in survival in resected stage III melanoma patients, especially using adjuvant agents with low morbidity and low cost.

**1.2. Surgery can suppress immune competence and promote cancer metastasis**

Surgery is life-saving and indispensable, but there have been suggestions that resection of a tumour may increase the risk of metastases for several reasons. It is possible that tumour cells may be shed during physical manipulation of the tumour during surgery^2-5^, or that release of growth factors^6,7^ and pro-angiogenic factors^8-10^ after tissue damage may promote the development of micrometastases. Immune suppression is also present postoperatively, in particular cell mediated immunity with suppression of natural killer cells and cytotoxic T lymphocytes^11,12^ . The perioperative immune suppression appears to correspond to the extent of surgical trauma and tissue damage^13^.

### **1.3. COX-2, catecholamines and carcinogenesis**

### Pro-inflammatory stress responses (especially following surgery) such as production of prostaglandins and catecholamines are linked to promotion of cancer metastasis, by release of angiogenic factors, stimulation of epithelial to mesenchymal transition and suppression of antitumour immunity^14^.

Cyclooxygenase-2 (COX-2) is generally upregulated only in pathological conditions such as inflammation and cancer. The main effects of COX-2 appear to be related to increased prostaglandin production, especially PGE_2,_ which significantly contributes to the induction of inflammation, and tumorigenesis. This has in turn been linked to the simulation of angiogenesis, inhibition of apoptosis, increased cell proliferation and immunosuppression^15-17^ which all assist carcinogenesis. PGE_2_ appears to be upregulated during and after surgery^18^.

**β1**and **β2** adrenoceptors are expressed by several human tumour lines, and catecholamines are potent direct stimulator of migration of some human carcinoma cell types (e.g. colon, breast and ovary) and of secretion of pro-angiogenic factors by these tumours^10,19-21^. Surgical manipulation and accompanying stress responses have been shown to be major suppressors of antimetastatic host cell mediated immunity e.g. cytotoxic activity of natural killer cells decreases following surgery^22^.

Controlling exaggerated inflammatory responses (with COX-2 inhibitors) and physiological (and psychological) sympathetic responses (with **β** blockers) could contribute to prevention of tumour metastatic development^22^. The use of COX-2 inhibitors could also improve postoperative pain and the use of **β** blockers could also assist in decreasing stress and anxiety in patients awaiting surgery.

### **1.4. β blockers and melanoma**

There is a suggestion that norepinephrine, a stress hormone produced after activation of the sympathetic-adrenal-medullary axis might play a role in the aetiology of some types of cancer, melanoma included^23^. It appears to upregulate tumour progression factors in melanoma cell lines^24^ and the use of β blockers in other cancers and in melanoma appears to attenuate the risk of disease progression.^25-27^

**1.5. COX-2 inhibitors and melanoma**

### UV damage of the skin appears to be related to DNA damage and COX-2 mediated PGE_2_ activity^28^. The simulation of angiogenesis, inhibition of apoptosis, increased cell proliferation and immunosuppression linked to COX-2 may promote melanoma initiation and progression^15,16,17^.

The main effects of COX-2 in melanoma appear to be related to PGE_2_ production which appears to contribute to invasion and progression of disease^15^. These are closely linked to the mitogen-activate protein kinase (MAPK) pathway which is a target for BRAF and MEK melanoma drugs^29^. COX-2 expression in melanoma also positively correlates with programmed death-ligand 1 (PD-L1) expression in BRAF mutated melanomas via IL-1 upregulation^30,31^. High PD-L1 expression in many cancers correlates with a bad prognosis, but for melanoma this is controversial.

COX-2 has also been identified as a potential marker for prognosis in melanoma. It has been found to be more markedly expressed in metastatic, poorer prognosis primary melanomas^32-34^ and has been associated with poor prognostic histopathological features like increased Breslow thickness, presence of ulceration and higher mitotic rate^33,35^. COX-2 has an intense expression at the centre of the tumour, with reduced COX-2 at the periphery.

COX-2 may therefore potentially be a therapeutic target in the treatment of melanoma. COX-2 activity can be inhibited by nonsteroidal anti-inflammatory drugs such as naproxen or indomethacin (nonselective inhibition as they also suppresses COX-1 activity) and selective inhibitors like celecoxib (brand name Celebrex)^36^. COX-2 inhibitors have little or no effect on coagulation and are therefore attractive for use in the surgical setting^37^.

### **Table 1** (from Tudor et al^38^) showing the main COX-2 inhibitors tested in melanoma and their effect as possible therapeutic adjuvants.

[figure not shown]

**1.6 Links between psychological stress and immunity**

Chronic psychological stress is associated with neuroendocrine and sympathetic nervous system activation and with suppression of anti-tumour immunity (reviewed by Hong et al)^39^.

### **1.7. Rationale for performing this study**

Despite the availability of systemic immune therapies for metastatic melanoma, such as PD1 inhibitors and ipilimumab, complete response occurs only in a minority of patients. Haldar et al^40^ administered oral propranolol (a β blocker) and the COX-2 inhibitor etodolac for 5 preoperative and 15 postoperative days in patients with colorectal cancer. Compared to patients receiving placebo, patients receiving the propranolol/etodolac combination showed significant changes in tumour markers for epithelial to mesenchymal transition and tumour immune markers. Tumour recurrence rates at 3 years postoperatively were non significantly reduced in the intervention arm (0/11 recurrences with treatment versus 5/17 recurrences with placebo in treatment-compliant patients).

Addition of a brief perioperative regimen of COX2 inhibitor and propranolol (using clinically feasible doses equivalent to those used by Haldar for colorectal cancer) could potentially improve anti-tumour immunity and effect long term influence on recurrence risk. This study will determine whether there are signals for enhanced anti-tumour immunity and reduced proliferation in patients with resected stage III melanoma receiving the ProCel regimen. This data could then be used to inform the design of larger randomised controlled clinical trials.

**2. HYPOTHESIS**

We hypothesise that perioperative administration of the ProCel regimen will alter the tumour immune environment, with reduced immune suppression, and will reduce tumour proliferative markers such as Ki67. We hypothesise that patients receiving the perioperative ProCel regimen will have lower levels of inflammatory markers and elevated markers of immunity in blood postoperatively, and lower circulating tumour DNA 4 months postoperatively, providing a signal that ProCel may reduce recurrence risks and improve outcomes in patients with metastatic melanoma.

# **3. STUDY OBJECTIVES**

### **3.1. Primary Objective/ primary endpoint**

To determine the effect of perioperative propranolol and celecoxib on intra-tumoral and peritumoral immune cell populations and proliferative markers, in patients with melanoma metastatic to nodes and/or in transit disease.

### **3.2. Secondary Objectives/ endpoints**

The secondary objectives are to determine the effect of the ProCel regimen on

3.2.1 Safety and tolerability (adverse events)

3.2.2 Serum inflammatory markers at D14 postoperatively (D20-D27)

3.2.3 Quality of Life, perceived stress and state (modifiable) optimism at D14 and at 4 months postoperatively, and correlation with baseline and postoperative blood and tumour inflammatory and immune markers.

3.2.4 Evidence of disease recurrence/progression at 4 months postoperatively in the 2 arms (based on staging investigations performed as part of routine clinical care. This usually includes PET-CT and brain imaging 3-4 monthly postoperatively and this data will be available for patients in both arms of the study.

# **4.** **STUDY PARTICIPANTS**

This study will be conducted through the Department of Melanoma and Surgical Oncology at Royal Prince Alfred Hospital and Poche Centre, North Sydney. Participants will be attendees of the clinics who require surgical management of their stage III metastatic melanoma.

### **4.1. Inclusion Criteria**

There will be NO EXCEPTIONS to eligibility requirements at the time of randomisation. Questions about eligibility criteria should be addressed PRIOR to enrolment.

Participants must meet ALL of the following inclusion criteria:

4.1.1 Aged 18 years or older, but not older than 85 years

4.1.2 Known metastatic cutaneous melanoma in lymph nodes and/or in transit recurrences in skin, measuring at least 0.5cm in largest diameter, appropriate for surgical management and where surgery is expected to render the patient clinically disease free.

4.1.3 Willingness and ability to provide informed consent and willingness to participate and comply with the study requirements.

### **4.2. Exclusion Criteria**

4.2.1 Unable to follow up for the duration of the study due to frailty, geographical or social reasons

4.2.2 Pregnant or lactating (women of childbearing potential must use appropriate contraception)

4.2.3 Known allergy to one or more of the study medications

4.2.4 Known contraindication to β-blockers (including hypersensitivity; unstable angina; severe asthma; bronchospasm predisposition; symptomatic hypotension; severe heart failure, moderate to high grade conduction disease, bradycardia <50 beats per minute, sick sinus syndrome, severe cardiomegaly, phaeochromocytoma)

4.2.5 Known contraindication to celecoxib (NSAID associated asthma or urticaria; concomitant NSAIDs (excluding low dose aspirin); active peptic ulcer with GI bleed; eGFR <30mls/min; renal impairment with eGFR<30mL/min

4.2.6 Patient already taking a β blocker, COX2 inhibitor (excluding low dose aspirin; ie ≤150mg daily), or digoxin within one month of study entry

4.2.7 Immune suppression (including transplant recipients, chronic haematological malignancies, immune-suppressive medications for autoimmune disorders)

4.2.8 Internal malignancy (other than metastatic melanoma) within the past 5 years

4.2.9 Current use of non-dihydropyridine calcium channel blockers (verapamil or diltiazem) or amiodarone

4.2.10 Current use of anti-platelets agents (aside from aspirin) i.e. P2Y12 antagonist (clopidogrel, ticagrelor or prasugrel)

4.2.11 Liver failure (cirrhosis)

4.2.12 Treatment with systemic immunotherapy (ipilimumab and/or PD1 inhibitor) within 4 weeks of surgery

# **5. STUDY PROCEDURES**

### **5.1. Participants N = 40 e**ligible patients with nodal and/or in transit metastatic melanoma randomised 1:1 to ProCel regimen or control, with stratification by tumour site (nodal disease ± skin or skin metastases only), and history of systemic immunotherapy or not. Eligibility will also be dependent on a baseline ECG with cardiologist ECG review confirming suitability for, and no ECG contraindications to, oral propranolol.

### **5.2. Investigation Plan**

Eligible participants randomised to ProCel will receive propranolol in combination with celecoxib for five days preoperatively, day of surgery and for 14 days postoperatively:

The study drugs will be sourced through the RPA Investigational Drugs Unit pharmacy.

**Celecoxib:** 200 mg/bd D1-20 [equivalent to etodolac 400bd]; participants will be provided with two bottles of 30 x 200mg tabs

**Propranolol:** participants will be provided with two bottles of 100 x 10mg tablets

D1-D2 Propranolol 20mg bd

D3-D5 Propranolol 40mg bd

D6 ***SURGERY***  Propranolol 60mg bd

(baseline blood pressure, heart rate recorded preoperatively on day of surgery; anaesthetist review preoperatively on day of surgery as per standard clinical care)

D7-D13 (D13=7 days postop)Propranolol 40mg bd

D14-D20 (D20=14d postop) Propranolol 20mg bd

(wound review and tablet adherence assessment at D20)

Participants will be provided with a pulse oximeter to record their heart rate each day. If heart rate is <60 beats per minute, participants are advised to continue the current dose, not increase the dose, and to notify the research team. If participants experience dizziness or shortness of breath, they are advised to stop taking propranolol, and to notify the research team. If the treating anaesthetist determines heart rate and blood pressure are too low for safe anaesthesia, surgery will not proceed.

Excised tumour will be used for routine histopathology, as well as for marker studies using imaging mass cytometry to assess tumour immunology and proliferation. This technique enables assessment of approximately 40 immune, proliferation and angiogenesis and apoptosis markers in each 1mm tissue core. Markers may include, but need not be limited to, markers such as B2M-c, CD11c, CD14, CD141, CD163, CD16a-c, CD1c-c, CD20, CD27-c, CD31, CD34, CD38, CD39, CD3e, CD4, CD45, CD45RO, CD68, CD8, CollagenIV, FOXP3, GZMB, HLA-A, HLA-DR, HLA-E, ICOS, IDO1, Ki-67, LAG3, MITF-c, MLANA-c, PD-1, PD-L1, PMEL-c, S100B-c, SMA, SOX10-c, TBET-c, TCF7-c, TIM3-c, Vimentin and VISTA.

Routine blood samples will be taken 5-28 days preoperatively (before the start of ProCel treatment) for routine testing (full blood count, electrolytes, creatinine, liver function tests and any other bloods that are clinically relevant for individual participants, eg coagulation studies) and also for blood inflammatory and immune markers.

Tumour mutation profiles (BRAF, NRAS) are routinely collected and this information will be examined in control and ProCel arms.

At D15 postoperatively (=D20; range D19-D26), participants will have a blood sample taken for serum inflammatory and immune markers as well as postoperative full blood count, electrolytes, liver function tests and creatinine. Imaging and clinical and histological evidence of recurrence at 4 months postoperatively will be collected as per routine clinical practice.

Participants with metastatic melanoma will be followed up with routine imaging, bloods and clinical examination as per standard clinical practice. Longer term follow-up information looking at recurrence rates in participants will thus continue to be collected in the medium to long term as part of clinical practice.

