**Protocol Compliance**

Drug intake and adherence will be monitored by a clinical research coordinator, based on patient reports and counting of unused tablets.

| **Investigation/intervention** | **Timing (Study Day)** | **Notes** |
| --- | --- | --- |
| Informed consent | At/ before D0 | Baseline |
| Inclusion/exclusion criteria | At/before D0 | Baseline |
| Medical History | At/before D0 | Baseline |
| ECG | At/Before D0 | Baseline; for cardiologist review prior to randomisation |
| Concomitant medications | At/before D0 | Baseline; medications checked and any changes noted at each visit |
| Blood sample collected | D0 (or up to 4 wks prior) | Baseline blood sample (total 40mL): for inflammatory and immune markers as per MIA biobank protocol (32mL) plus routine preoperative bloods (FBC, EUC, LFTs*; 8mL). |
| QoL, perceived stress and state optimism scales | D0 |  |
| Nodal and/or skin metastases biopsied (2 x 2mm^2^ core biopsies for diagnosis and for tissue microarray | 28-14 days before D0 |  |
| ProCel treatment | D0 | Commenced 5d preoperatively: (D0) |
| Tumour assessment (IHC) | D6 | Excision specimens obtained after 5d of ProCel regimen and controls (D6 = day of surgery) |
| Blood sample collected | D20 (range D20-D27) | Postoperative bloods collected D20 (range D20-D27; ie 2 to 3 wks postoperatively) for inflammatory and immune markers as per MIA biobank protocol (32mL) and routine postoperative bloods (FBC, EUC, LFTs; 8mL) |
| QoL, perceived stress and state optimism scales | D20 (range D20-D27) |  |
| Adverse events | During and for 30 days after ProCel regimen | D6 (day of surgery), D20 (postop followup), D45 (30 days after ceasing medication) |
| Clinical and radiological followup | 4 months postoperatively (range 3-5 months) | Clinical review and surveillance imaging as per standard clinical practice |
| QoL, perceived stress and state optimism scales | 4 months postoperatively(range 3 – 5 months) | Performed at the time of 4 month postoperative review |

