# **6. SAFETY**

Adverse events will be recorded at each visit and graded using the NCI Common Terminology Criteria for Adverse Events Version 4.0 (CTCAE).

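### Section 5.2, read in context, gives home heart-rate monitoring and a symptom call-in instruction to the ProCel arm only, so the arm comparison of low heart rate, dizziness and breathlessness may be biased toward more events on ProCel

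*Protocol*

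**What the plan says.** Section 5.2 (Investigation Plan) opens with patients randomised to ProCel and sets out their drug supply and day-by-day doses. It then states "Participants will be provided with a pulse oximeter to record their heart rate each day". A participant with a rate below 60 is told to keep the current dose, not raise it, and notify the research team. One with dizziness or shortness of breath is told to stop propranolol and notify the team. A few lines earlier the same word is used for the drug supply: "participants will be provided with two bottles of 30 x 200mg tabs".

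For adverse events in general, section 6 says "Adverse events will be recorded at each visit and graded using the NCI Common Terminology Criteria for Adverse Events". The schedule table under Protocol Compliance lists the time points as "D6 (day of surgery), D20 (postop followup), D45 (30 days after ceasing medication" and defines the collection window by the ProCel regimen.

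The lead-in to section 3.2 reads "The secondary objectives are to determine the effect of the ProCel regimen on", and its first item is "3.2.1 Safety and tolerability (adverse events". The Study Design summary states that "blinding is not possible for treating clinicians or participants".

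**The concern.** Adverse-event counts in two arms can be compared only if events are looked for in the same way in both. Here one arm appears to have a device, a daily reading and a standing prompt to call in, and the other has visit-based recording alone. The prompted events are the ones that the protocol itself links to propranolol, so any distortion has a predictable direction: more such events found on ProCel at equal true risk. Because participants and treating clinicians know the allocation, blinding does not offset this.

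At stake is the tolerability contrast. Section 1.7 says that the data could inform larger randomised trials, so a distorted contrast could be carried forward. Analysis cannot repair it afterwards, because control events that were never elicited are not in the data.

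**Working it through.** **Step 1. Which arm has the monitoring?** The oximeter sentence says only participants. Three features of section 5.2 point to ProCel alone: it follows the ProCel supply and dose schedule; the same word in the drug-bottle sentence can only mean ProCel patients; and both notification instructions are responses to a propranolol dose, which a control does not take. No sentence says that controls get no oximeter, so for the device this is an inference from context. The notification instructions, as worded, can work only in the ProCel arm.

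**Step 2. What is written for controls?** Visit recording under section 6 and the D6, D20 and D45 entries of the schedule, neither of which distinguishes the arms. No home reading or call-in instruction appears for controls.

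**Step 3. Can the extra readings pick up something other than a drug effect?** Yes. Section 4.2.4 excludes bradycardia below 50, while notification is triggered below 60. A patient with a resting rate of 50–59 before any drug is eligible and would meet the notification rule on ProCel. The same patient in the control arm has no daily reading.

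**Step 4. Size.** The protocol gives no event rates and no figure to reproduce. The inputs that it does give are 20 dosing days, two visits in that period (D6, D20), and "N=40; randomised 1:1 to ProCel or control arms", that is 20 per arm. Everything else below is assumed.

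(a) Low readings. Days without a scheduled reading in controls: (20 − 2)/20 = 90%. Let q be the daily chance of a reading below 60 without drug, with days independent. The chance of at least one such reading is 1 − (1 − q)^20 with daily readings and 1 − (1 − q)^2 with two visit readings.

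| q (assumed) | 20 daily readings | 2 visit readings |
| --- | --- | --- |
| 1% | 18% | 2% |
| 2% | 33% | 4% |
| 5% | 64% | 10% |
| 10% | 88% | 19% |

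These are readings, not adverse events, and independence makes the gap large. At the other extreme, where a low rate is a fixed trait of the patient, one visit reading would find it as surely as 20 home readings and the gap would vanish.

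(b) Events. Let the true risk p be equal in both arms, capture be complete on ProCel, and a fraction s of control events be captured. The apparent risk ratio is p/(ps) = 1/s. With 20 per arm and p = 30% (assumed), the expected counts are 20 × 0.30 = 6 on ProCel and 6s on control. The last column is the exact chance of a two-sided Fisher p < 0.05. The protocol names no test, so Fisher's test is used for illustration.

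| s (assumed) | Expected counts, ProCel v control | Apparent risk ratio | Chance of p < 0.05 |
| --- | --- | --- | --- |
| 100% | 6 v 6 | 1.00 | 2.5% |
| 75% | 6 v 4.5 | 1.33 | 4.4% |
| 50% | 6 v 3 | 2.0 | 12.4% |
| 25% | 6 v 1.5 | 4.0 | 33.1% |

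At s = 50% the last column runs from 1.7% (p = 10%) to 19.2% (p = 40%). In a trial of this size the main harm is a distorted estimate rather than a false significant result.

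**The case against.** The strongest objection is that the protocol does not say what a reader might infer: that bradycardia, dizziness and dyspnoea are over-counted on ProCel. No passage makes a home reading or a call an adverse event; a rate below 60 triggers a notification, and section 6 records events at visits in both arms. This stands. The bias is possible and its direction is predictable, but it is not established. It could equally be correct counting on ProCel with under-counting in controls. The silence is no safeguard either, since no rule keeps these reports out of the counts.

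Second, the comparison may be thinner than it looks. The Summary words the safety objective without a comparator, whereas the blood-marker objective beside it names controls; item 3.2.4 mentions both arms and 3.2.1 does not. If safety is purely descriptive, fuller capture on ProCel is an advantage. This stands in part. The section 3.2 lead-in still speaks of an effect of the regimen in a randomised controlled study, and an effect needs a comparator.

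Third, some collection is already common to both arms: visit recording, and the QLQ-C30 item on shortness of breath over the past week, given at baseline, D20 and 4 months. This helps for breathlessness, but it is a quality-of-life item and not an adverse-event record.

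Fourth, checklists and form fields are often left to the case report form or the SAP. That is fair for table layout. It does not reach unequal collection, which follows from the conduct that the protocol lays down.

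Finally, closer monitoring of treated patients is a natural safety measure, and taking home-detected events out of the by-arm tables could understate harm. Both points are accepted: the monitoring is not questioned, and no event should leave the by-arm listing.

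**Conclusion.** The point holds as a risk of differential ascertainment. As written, section 5.2 gives the ProCel arm a means of detecting low heart rate, dizziness and breathlessness that has no written equivalent for controls, in an open-label trial whose section 3.2 frames adverse events as an effect of ProCel. The comparison of those three events may therefore lean toward more events on ProCel. Other adverse events are not touched by this argument.

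The conclusion rests on reading the oximeter sentence in context as ProCel-only, and on home reports finding their way into the adverse-event record. The size cannot be stated from the documents. It would be a mistake to take 18–88% against 2–19% as an estimate of bias: those figures count readings on an assumed rate with independent days, and they say nothing about dizziness or breathlessness. The change is worth making because it is cheap and cannot be made retrospectively, but this is a secondary endpoint of a 40-patient pilot and does not threaten the primary objective.

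**What to change.** - **Section 5.2:** state which arm has the home monitoring and the call-in instruction, and whether a home reading or a call is entered as an adverse event.
- **Section 6 and the schedule table:** elicit adverse events in both arms at the same existing contacts (D6, D20 and the final safety contact), with the same symptom questions, including dizziness and shortness of breath, and a heart rate. The day of the final contact also needs reconciling: the table labels D45 as 30 days after ceasing medication, but the last dosing day in section 5.2 is D20, and 20 + 30 = 50.
- **Adverse-event form:** add one field for how the event was first detected.
- **Section 3.2.1:** base the arm comparison for these three events on those elicited by the common questions and the contact heart rate. Keep all events from every source listed by arm, and flag those found only through home monitoring as descriptive ProCel-only data.

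The cost is protocol wording, a short checklist at contacts that already exist, and one form field. The comparative counts for these events may be lower than the all-source counts, so both should be shown. Some imbalance will remain, because ProCel patients know their allocation and have been alerted to these symptoms. The monitoring and dosing instructions are unchanged.

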### **5.3. Participant Recruitment and Enrolment**

Participants will be recruited from the Melanoma and Surgical Oncology clinics at RPA Hospital and Poche Centre. Potential participants, who meet all inclusion and no exclusion criteria will be provided with the participant information statement and consent form at their first appointment. Participants will have at least one week until their next appointment to consider whether they wish to participate. Participants who complete the informed consent process appropriately with their treating clinician at their second appointment will be enrolled in the study. Potential participants will have medical and medication history, blood pressure, heart rate and ECG reviewed by a cardiologist prior to randomisation to ensure their suitability for the study.

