### **5.5. End of Study Intervention and Withdrawal Procedure**

**5.5.1 Criteria for Treatment Cessation**

Participants may cease to take part in the study in the following circumstances:

- Intercurrent illness which would, in the judgement of the investigator, affect assessments of clinical status to a significant degree, and require discontinuation of protocol therapy.
- Unacceptable toxicity or reaction.
- Participation in this study is voluntary; participants are able to withdraw at any time. Those who withdraw from the study will be asked to continue to attend follow up visits, as per routine clinical practice, to allow the collection of outcome data and to enable appropriate ongoing clinical management and follow up. If a participant decides to stop their follow up visits, their health status will be periodically ascertained via phone contact with their referring doctor or by direct phone contact with the patient.
- Completion of therapy. Efforts should be made to maintain the investigations schedule and continue follow up, even if patients discontinue protocol treatment prematurely and/or no longer attend the clinic.

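### Section 5.2 sets no heart rate at which propranolol is withheld, so a symptom-free participant below 50 beats per minute is advised to keep dosing until the research team responds

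*Protocol*

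**What the plan says.** Section 5.2 raises propranolol from 20 mg twice daily (D1-D2) to 40 mg (D3-D5) and 60 mg (D6, surgery), then lowers it to 40 mg (D7-D13) and 20 mg (D14-D20). Monitoring at home is by the participant: "Participants will be provided with a pulse oximeter to record their heart rate each day".

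Two instructions to the participant follow.

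- By rate, when the measured "rate is <60 beats per minute, participants are advised to continue the current dose, not increase the dose, and to notify the research team".
- By symptom: "If participants experience dizziness or shortness of breath, they are advised to stop taking propranolol", and again to notify the team.

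Among the contraindications to β-blockers at entry, section 4.2.4 lists "bradycardia <50 beats per minute".

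Other safeguards are stated elsewhere. Section 5.3 has "heart rate and ECG reviewed by a cardiologist prior to randomisation". Section 5.2 provides for "anaesthetist review preoperatively on day of surgery as per standard clinical care", and surgery is called off if the anaesthetist finds heart rate and blood pressure too low. Section 5.5.1 allows cessation for "Unacceptable toxicity or reaction".

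**The concern.** The rate rule treats 58 and 42 alike. A protocol may leave bradycardia to clinical judgement, but this text tells the participant what to do before any clinician has judged, and the advice is to stay on the drug. The one figure the protocol gives for a rate too slow for a β-blocker, 50, plays no part once treatment has begun.

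The rule also cannot mark a worsening. Section 4.2.4 excludes only rates below 50, so someone at 50-59 can enter if the cardiologist agrees, and may meet the below-60 rule from the first day. A later fall from 55 to 45 changes nothing in the written advice.

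At stake is the safety of participants at home, who may be up to 85 years old (4.1.1). The primary tissue comparison is little affected.

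**Working it through.** **1. Is there a hold level anywhere?** Reading each relevant section for a heart rate at which propranolol is withheld or reduced during treatment:

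| Place | What it provides | On-treatment hold rate? |
| --- | --- | --- |
| 4.2.4 | entry limit, below 50 | no, entry only |
| 5.1, 5.3 | cardiologist review before randomisation | no |
| 5.2, rate rule | below 60: same dose, no increase, notify | no lower limit |
| 5.2, symptom rule | stop on either of two symptoms | no, symptoms only |
| 5.2, day of surgery | anaesthetist decides whether surgery goes ahead | no number, and not a dosing rule |
| 5.2, schedule table | adverse events at D6, D20, D45 | no |
| 5.5.1 | cessation for toxicity | no number |
| 6 | grading and reporting of adverse events | no |
| 10 | heart rate among baseline data for the monitoring board | no |

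**2. Test case.** A participant without symptoms reads 45. Since 45 < 60, the rate rule applies. Since 45 < 50, the reading is in the range that 4.2.4 bars at entry. The symptom rule is not met. The written advice is to stay on the same dose and notify. No response time or action by the team is stated. Between surgery and D20 no adverse-event assessment is scheduled, so the participant's own reading and this rule are the main listed heart-rate safeguard.

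**3. How much drug is taken while waiting?** Scheduled daily dose: 2 × 20 = 40 mg, 2 × 40 = 80 mg, 2 × 60 = 120 mg. The bar on increases limits what can be reached. This assumes that the reading is taken before a step-up dose and that the scheduled reductions still apply.

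- Below 60 before D3: the D3 step is barred, so 40 mg per day.
- First below 60 during D3-D5: the D6 step is barred, so 80 mg per day.
- First below 60 after the first 60 mg dose on D6: one further 60 mg dose that day.
- D7-D13: at most 80 mg per day. D14-D20: 40 mg per day.

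**4. How many participants?** The protocol gives no frequency. About 40 / 2 = 20 are planned for ProCel. Assumed shares of 1%, 5% and 10% with a symptom-free rate below 50 give 20 × 0.01 = 0.2, 20 × 0.05 = 1 and 20 × 0.10 = 2 participants. These figures only restate the assumption, and they count readings, not harm.

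**5. What would withholding cost in dose?** Full course: D1-D2 2 × 40 = 80; D3-D5 3 × 80 = 240; D6 120; D7-D13 7 × 80 = 560; D14-D20 7 × 40 = 280. The total is 80 + 240 + 120 + 560 + 280 = 1280 mg.

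- One withheld dose: 20/1280 = 1.6%, 40/1280 = 3.1%, 60/1280 = 4.7%.
- Before the day of surgery: 80 + 240 = 320 mg, so one withheld dose is at most 40/320 = 12.5%.

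**The case against.** The strongest reply is that the rule already acts early and hands the decision to clinicians. Its trigger is 10 beats above the entry limit, it bars escalation, and it requires notification. Daily readings, a symptom stop, day-of-surgery review and a general cessation criterion support it. Participants are screened by a cardiologist, and those with significant conduction disease or on digoxin, verapamil, diltiazem or amiodarone are excluded. A slower pulse is an expected effect of propranolol, so an entry limit for untreated patients need not be the right limit on treatment. Interrupting a β-blocker around surgery on one home oximeter reading has its own drawbacks.

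Much of this stands. It makes the gap small, leaves the choice of 50 open to the cardiologist, and calls for a repeat reading before a dose is withheld. It does not supply a hold level, and it does not change what the participant is advised to do in the interval before anyone answers.

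Three stronger readings are tempting, and the protocol does not support them.

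- A reader might infer that 5.2 contradicts 4.2.4. It does not: one governs entry and the other dosing during treatment.
- A reader might take exposure while waiting as the full 120 mg of D6. The no-increase rule prevents that for anyone already below 60, and D6 is the day on which the anaesthetist sees the patient.
- A reader might infer that participants would wait long for an answer. Nothing in the text says so, and the full participant instructions are not shown.

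**Conclusion.** The point holds as a modest patient-safety gap in the wording of 5.2, and it should be fixed because the fix is cheap. Followed exactly, the rule keeps a symptom-free participant on propranolol at a rate that would have barred entry, for as long as the team takes to respond.

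The conclusion on the text needs no assumption. The size rests on three: the step-up bar is followed, the scheduled reductions continue below 60 (5.2 does not say so expressly, but nothing suspends them), and some participants do fall below 50 without symptoms, in a number that cannot be derived from the protocol. What the team would do once notified may be set out in working instructions, so the finding concerns the written rule and not the care that would actually be given.

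**What to change.** Amend 5.2 and the participant instructions to two tiers.

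1. At 50-59: do not increase the dose, and notify the research team. The scheduled D7 and D14 reductions still apply.
2. Below 50, confirmed by a repeat resting reading: withhold the next propranolol dose and contact the team the same day. The cardiologist decides on restart or dose, together with the anaesthetist on D6.

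The level of 50 is proposed because 4.2.4 already uses it. The study cardiologist may confirm or change it.

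The cost is a few sentences and no extra visits, using readings that are already collected. The downside is a few withheld doses, of the sizes worked out above, and a brief perioperative interruption of the drug in a few participants.
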